**1.8 Safety Considerations and Drug administration.**

The most clinically relevant side effects to zoledronic acid include impaired renal function, hypocalcaemia, and BON. Because of this, evaluation of renal function and supplementary intake of calcium +/- vitamin D should be conducted in accordance with local guidelines. During the study, serum creatinine and ionized calcium will be measured monthly and recorded in the CRF.

Risk of BON

Concerning BON, patients should receive a thorough dental examination prior to treatment initiation if possible, maximal dental hygiene should be maintained and conservative approaches should be applied if dental problem arises. Oral investigation will be conducted at least once a year in the first two years and every 3 months from year 2 to 4 by the treating physician in order to detect any cases of BON. All cases of BON will be recorded in the CRF. All cases of BON will be reported annually to the sponsor. In case of BON, it is up to the treating physician to decide if it is in the best interest of the patient to remain on bisphosphonate treatment or if treatment should be stopped, in which case the patient is excluded from the study.

In case dental problems arise, they shall if possible be treated conservatively. No data exists as to whether zoledronic acid should be withheld or continued if tooth extraction cannot be avoided. If the treating clinician finds in the best interest of the patient, infusion with zoledronic acid may be withheld up to one month prior to tooth extraction, and up to maximum three months after tooth extraction, thus allowing a four-month pause in total from zoledronic acid treatment. It is recommended however that the patients receive prophylactic antibiotic in case tooth extraction cannot be avoided [[12](#_ENREF_12)].

Risk of PBD

Zoledronic acid is administrated to the patients in order to minimise the risk of PBD. In this study, we want to evaluate if the potential benefit of prolonged zoledronic acid treatment outweigh the increased risk of BON. To minimise the risk of undetected PBD we will from year 2 to 4 conduct regular bone imaging every 3 month. Furthermore, it is mandatory to conduct bone imaging in case of progressive myeloma disease requiring treatment. To further improve the safety of the patients we have invented a less rigours event definition (PDB) compared to the more strict definition (sPBD) where the progression have to be symptomatic to be calculated as an event. All cases of sPBD will be reported annually to the sponsor.

Radiation exposure:

The following text applies to patients in which evaluation of bone disease is conducted with both conventional radiography and low-dose CT, thus it is the patients who receive the highest radiation dose.

Scheduled bone imaging will be conducted seven times during the four years period. Perhaps one extra bone imaging will be conducted in case of relapse from year 2-4. This equals a total radiation dose of 45.5-52 mSv. A patient not included in the study would probably within the same time frame have approximately three conventional radiography and 1-2 low dose CT conducted, equal to a total radiation dose of 11.3-15.4mSv. The patients will over a four years period receive an excess radiation dose of 33.2-36.6, which is equivalent to the dose received from 1.5 conventional CT. The additional bone imaging will not only be conducted for scientific reasons, but also to make sure no serious progressive bone disease occurs when the patient is not receiving zoledronic acid.

Drug administration and renal function

Four mg of zoledronic acid will be administered intravenously at the hospital every fourth week (+/- 1 week) according to local instructions, for either two or four years.

If no local instruction exists, please see the Summary of Product Characteristics at EMEA. In brief it states: *zoledronic acid 4 mg should be given as a single intravenous infusion in no less than 15 minutes. To prevent hypocalcaemia patients should also be administered an oral calcium supplement of 500 mg and 400 IU vitamin D daily. When initiating treatment with zoledronic, serum creatinine and creatinine clearance (CLcr) should be determined. CLcr is calculated from serum creatinine using the Cockcroft-Gault formula. Zoledronic is not recommended for patients presenting with severe renal impairment prior to initiation of therapy, which is defined for this population as CLcr < 30 ml/min. In patients presenting with mild to moderate renal impairment defined as CLcr 30–60 ml/min, the following zoledronic acid dose is recommended:*

| **Baseline creatinine clearance (ml/min)** | **Zoledronic acid recommended dose*** |
| --- | --- |
| > 60 | 4.0 mg zoledronic acid |
| 50–60 | 3.5 mg* zoledronic acid |
| 40–49 | 3.3 mg* zoledronic acid |
| 30–39 | 3.0 mg* zoledronic acid |

- Doses have been calculated assuming target AUC of 0.66 (mg•hr/l) (CLcr = 75 ml/min). The reduced doses for patients with renal impairment are expected to achieve the same AUC as that seen in patients with creatinine clearance of 75 ml/min.

*Following initiation of therapy, serum creatinine should be measured prior to each dose of zoledronic acid and treatment should be withheld if renal function has deteriorated. In the clinical trials, renal deterioration was defined as follows:*

*- For patients with normal baseline serum creatinine (< 1.4 mg/dl or < 124 μmol/l), an increase of 0.5 mg/dl or 44 μmol/l;*

*- For patients with abnormal baseline creatinine (> 1.4 mg/dl or > 124 μmol/l), an increase of 1.0 mg/dl or 88 μmol/l.*

*In the clinical studies, zoledronic acid treatment was resumed only when the creatinine level returned to within 10% of the baseline value. Zoledronic acid treatment should be resumed at the same dose as that given prior to treatment interruption.*

For further details see appendix 5.

If infusion of bisphosphonate for any reason is delayed for more that two months (meaning more that three months between two infusions) e.g. due to deteriorating renal function the patient will be excluded from the study.

Amendment:

Patients included according to the amendment will have a smaller radiation exposure 32.5-39 mSv instead of 45.5-52 mSv

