Fasting serum bone markers will be collected bi–annually. All time-points can be moved +/- 2 weeks.

Measurements of creatinine and calcium may be conducted up till 2 weeks before the visit

QoL questionnaire QLQ-C30 and MY20 will be used bi-annularly. All time-points can be moved +/- 2 weeks.

Infusion with zoledronic acid should be given ever 4^th^ week (+/- 1 week). Infusion can be delayed for up to 2 months e.g. due to temporarily impaired renal function (meaning a three month pause between two infusion is allowed). If infusions cannot be given within this time period the patient will be excluded from the study. If infusions are delayed for a significant period, it is the time passed and not the number of infusions that is relevant as to when stratification occurs.

Randomisation:

At year 2 patients will be randomised to A) stop treatment with zoledronic acid or to B) continue treatment with monthly infusions of zoledronic acid for another 2 years period (4 years in total). Randomisation is allowed to be moved -1months/+2months. The randomisation procedure will be stratified according to previous autologous stem cell treatment, presence or absence of bone disease at diagnosis, and previous treatment with bortezomib. Randomisation will take place at The Hematological Research Unit, Odense University Hospital, Denmark. For further details see appendix 6 (SOP for randomisation).

Planned visits, year 2-4:

Bone imaging will be conducted after 2½ years, after 3 years, after 3½ years, and after 4 years. All time-points can be moved +/- 1 month. In case of myeloma relapse requiring active treatment, new bone imaging should be conducted within a one-month time frame of initiation of new anti-myeloma treatment. If bone imaging has been conducted as part of relapse evaluation no less than three month prior to routine bone imaging time point,no new bone imaging need to be conducted. If any bone imaging, conducted from year 2 to 4, reveals PBD in patients not receiving zoledronic acid and the treating physician find it necessary to reinitiate treatment with zoledronic acid, the patient will be excluded from the study. In that case, fasting serum bone markers should be measured prior to re-initiation of zoledronic acid treatment. If bone imaging, conducted as part of a myeloma relapse evaluation in patients not receiving zoledronic acid, results in “no PBD”, treatment with zoledronic acid should *not* be re-initiated.

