Bone imaging should be conducted using both conventional radiography and low-dose CT. Sites however may participate in the study without conducting both conventional radiography and low-dose CT. In this case, the chosen modality must be used consistently throughout the entire study period.

Fasting serum bone markers should be collected every fourth week (+/- 1 week) throughout this period. Serum samples do not need to be collected at the exact date of zoledronic acid infusion but can be collected up to two weeks prior to infusion; serum samples however must not be collected after zoledronic acid infusion. Measurements of creatinine and calcium may be conducted up till 2 weeks before the visit

QoL questionnaire QLQ-C30 and MY20 will be used every 3^rd^ month: after 27, 30, 33, 36, 39, 42, 45, and after 48 months. All time-points can be moved -2 weeks.

Infusion with zoledronic acid in the treatment arm should be given ever 4^th^ week (+/- 1 week). Infusion can be delayed for up to 2 months e.g. due to temporarily impaired renal function (meaning a three month pause between two infusion is allowed). If infusions cannot be given within this time period the patient will be excluded from the study.

For specific instructions concerning conventional radiography and low-dose CT, see appendix 2

For specific instructions concerning serum bone makers, see appendix 3

Amendment:

Patients who are included after 23-25 zoledronic acid infusions outside protocol will move directly to randomisation. The randomisation procedure will be stratified according to previous autologous stem cell treatment, presence or absence of bone disease at diagnosis, and previous treatment with bortezomib. Randomisation will take place at The Hematological Research Unit, Odense University Hospital, Denmark. For further details see appendix 6 (SOP for randomisation).

Acquiring source data (amendment):

Bone imaging must not be done more than two months prior to inclusion and should be done no more than one month after inclusion.

Fasting serum bone markers must be collected no more that 2 weeks after inclusion.

QoL questionnaire QLQ-C30 and MY20 should be completed no more that 2 weeks after inclusion.

Investigation according to local guideline for any pre-existing BON must be conducted before inclusion in the protocol amendment

Planned visits, year 2-4: (amendment)

No changes compared to original description.

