**1.12 Withdrawal from the Study.**

In accordance with the current revision of the Declaration of Helsinki and applicable regulations, a

patient has the right to withdraw from the study at any time for any reason without prejudice to

his/her future medical care by the physician or at the institution.

Patients may be excluded from study in case of:

-significant protocol violation or non-compliance

-refusal of the patient to continue treatment and observations; withdrawal of consent

-if the investigator believes that for safety reasons (e.g., adverse events), it is in the best interest of the subject to stop treatment.

-if the patient due to renal failure is unable to receive zoledronic acid in two consecutive months (infusion can be delayed for up to three months). In case of tooth extraction, a delay of up to four months is allowed.

-if the patient due to BON stops treatment with zoledronic acid.

-if patients in the control arm experience progressive bone disease and the treating physician find it in the best interest of the patient to reinitiate treatment with zoledronic acid.

-if the subject becomes pregnant

-death

Patients excluded from the study will be followed for 30 days by the local hospital to insure registration of late occurring AE, SAE, SAR and SUSARs

The date and the reason for withdrawal status should be stated in the case report form. If the patient withdraws his or / her consent no further investigations will be conducted. If the patient is excluded for other reasons and it poses no risk for the patient fasting serum bone marker should be measured upon withdrawal, and bone imaging should be conducted no less than one month after withdrawal from the study. Data collected from the patient up until the time of withdrawal will if possible be used in the final evaluation of the study result unless the patient states it otherwise.

As stated in section 1.13, 286 patients need to be randomised to achieve enough power in the study. Patients will be included until this number is reached

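### The infusion-gap exclusion rule contradicts the tooth-extraction allowance: an extraction pause of more than three and up to four months is both permitted and a mandatory ground for exclusion

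*Protocol*

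**What the plan says.** **General limit.** Section 1.7 states it twice, for years 0-2 and for the treatment arm in years 2-4. An infusion may be "delayed for up to 2 months e.g. due to temporarily impaired renal function (meaning a three month pause between two infusion is allowed"), and "If infusions cannot be given within this time period the patient will be excluded from the study". Section 1.8, under Drug administration and renal function, repeats the limit and widens its scope: "If infusion of bisphosphonate for any reason is delayed for more that two months (meaning more that three months between two infusions"), with mandatory exclusion as the consequence.

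**Tooth extraction.** Section 1.8, under Risk of BON, lets the clinician hold back infusions for a month at most before an extraction and three months at most after it, and gives the total as follows: "thus allowing a four-month pause in total from zoledronic acid treatment". Section 1.12 says: "In case of tooth extraction, a delay of up to four months is allowed".

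**Renal failure.** Section 1.12 also lists as a ground for exclusion that the patient is "unable to receive zoledronic acid in two consecutive months (infusion can be delayed for up to three months"). The list in which this stands is introduced with *may*, whereas Sections 1.7 and 1.8 use *will*.

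**The concern.** These are working rules that sites apply, and an excluded patient largely leaves observation. Section 1.6 plans no protocol follow-up after a patient leaves. Section 1.12 leaves a withdrawal bone-marker sample and bone imaging where they pose no risk, and 30 days of adverse-event registration.

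After randomisation arm A receives no infusions, so an infusion-gap rule can remove only arm B patients. Section 1.13 analyses patients per protocol and by treatment actually received, and Section 1.15 confirms that the trial is not blinded. A site facing an extraction pause in the disputed range can cite the protocol for keeping the patient or for removing the patient.

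The extraction case also bears on a key secondary endpoint. Section 1.3 describes BON as common after extraction, and weighing PBD protection against BON risk is the stated purpose of the trial (Section 1.14). Section 1.5 requires exposed bone for more than 8 weeks (56 days) before BON is diagnosed, against 30 days of registration after exclusion. A BON that begins after exclusion cannot meet that definition within the window. One already present would have to have begun more than 56 - 30 = 26 days before exclusion.

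**Working it through.** No sample-size or power formula applies. The check is calendar arithmetic on the limits as written.

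**Step 1: the protocol's own conversion.** Gap between infusions = normal interval + delay = 1 + 2 = 3 months, as Sections 1.7 and 1.8 state. With the exact four-week interval and a month of 365.25/12/7 = 4.348 weeks, the gap is 4 + 2 × 4.348 = 12.70 weeks, or 12.70/4.348 = 2.92 months. The stated figure is reproduced to rounding. Sections 1.7 and 1.8 (Drug administration) agree with each other.

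**Step 2: the extraction allowance.** One month before + three months after = 4 months, as Section 1.8 (Risk of BON) states. I take pause to mean the time between two infusions, which is how Section 1.7 uses the word.

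**Step 3: the renal clause in Section 1.12.** Infusion given at month 0, missed at months 1 and 2, given at month 3: the gap is 3 months. That is exactly what Section 1.7 permits, yet two missed consecutive months are listed as a ground for exclusion. The bracket after the clause allows a three-month delay. By the Step 1 conversion that is 3 + 1 = 4 months between infusions; if delay there means the whole gap, it is 3 months.

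**Step 4: apply each rule to the same gap.** Section 1.12 is read both ways: delay as the whole gap, or delay plus the normal interval (extraction 4 + 1 = 5 months).

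| Reason and gap | 1.7 and 1.8 Drug administration | 1.8 Risk of BON | 1.12, delay = whole gap | 1.12, delay + 1 month |
|---|---|---|---|---|
| Extraction, 3 months | kept | kept | kept | kept |
| Extraction, 3.5 months | excluded | kept | kept | kept |
| Extraction, 4 months | excluded | kept | kept | kept |
| Extraction, 4.5 months | excluded | beyond allowance | beyond allowance | kept |
| Renal, 3 months | kept | not applicable | kept by bracket; meets two-month clause | kept by bracket; meets two-month clause |
| Renal, 3.5 months | excluded | not applicable | beyond allowance | kept by bracket; meets two-month clause |

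The rows for extraction at 3.5 and 4 months conflict whichever way Section 1.12 is read. The rows for extraction at 4.5 months and renal at 3.5 months turn on how Section 1.12 uses delay. The renal row at 3 months turns on whether the bracket explains the clause before it or stands apart from it.

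**Step 5: timing in the disputed range.** If the full month before extraction is used, the general limit is reached 3 - 1 = 2 months after the extraction, while the extraction rule still has a month to run.

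**The case against.** The best defence is that the extraction rule is plainly meant as an exception. It is the more specific rule, it stands in the same section as the any-reason sentence, and Section 1.12 places it directly after the renal rule. The any-reason sentence falls under a heading on renal function and gives renal deterioration as its example. On this view the only defect is a missing exception.

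That is a plausible account of the intent, but the text does not carry it. The any-reason wording rules out an implied exception, and neither statement in Section 1.7 provides one.

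Other parts of the defence do stand, and they limit the point. A reader might infer the following, which the protocol does not support:

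- **Four incompatible limits, reaching five months.** The five-month figure appears nowhere in the protocol. It comes from applying the conversion in Sections 1.7 and 1.8 to the differently worded Section 1.12. If delay there loosely means pause, two limits remain: three months in general and four for extraction.
- **Excluded patients vanish from the primary comparison.** Section 1.12 uses data up to withdrawal where possible, and Section 1.13 plans a Kaplan-Meier analysis, which can censor. What is lost is later observation.
- **Section 1.12 deliberately grants discretion.** Its *may* heads a list that includes pregnancy and death, so loose drafting is the likelier explanation. The verb still needs to agree with the other sections.
- **Every extraction is affected.** Withholding is optional under Section 1.8, so the core conflict concerns only pauses longer than three months.

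**Conclusion.** The contradiction stands on every reading. For an extraction pause of more than three and up to four months, Section 1.8 (Risk of BON) and Section 1.12 keep the patient, while Section 1.7 and Section 1.8 (Drug administration and renal function) require exclusion. The wording of Section 1.12 on renal gaps, on delay against pause, and on *may* against *will* is a secondary ambiguity.

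The certain conflict is one month wide. The number of patients in it, and any effect on the PBD comparison or the BON count, cannot be derived, because the protocol gives no frequency of extractions or long gaps. The conclusion assumes only that pause means time between infusions; if the extraction allowance implied a longer gap, the conflict would widen. Before randomisation the rule affects who reaches randomisation, but not one arm against the other. After it, only arm B is exposed. The matter cannot be left to an analysis plan, which cannot recover follow-up for a patient already removed.

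**What to change.** Reconcile Section 1.7 (both statements), Section 1.8 (Risk of BON, and Drug administration and renal function) and Section 1.12 into one rule:

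- Use one unit: time between two consecutive infusions.
- State explicitly whether tooth extraction is an exception to the any-reason exclusion, and use the same statement in every section.
- State the renal limit once, and remove the tension between the two-month clause and its bracket.
- Use one verb for the consequence.

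The sponsor's clinicians choose the limits; this review takes no position on them. Apply the reconciled rule prospectively. Do not reclassify past exclusions: follow-up already lost cannot be restored, and sorting patients again in an unblinded per-protocol trial could itself introduce bias. Instead, report exclusions for infusion gaps with their reason (renal, extraction, other), separately before and after randomisation.

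The cost is a wording amendment, with the approvals that Section 1.14 requires for amendments, and a clarification letter to sites. Section 1.12 already asks for the date and reason of withdrawal in the case report form, so the reporting should need little new data. Gaps handled before the change will remain inconsistent, and the report should say so.

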**1.9 Side Effects.**

Zoledronic acid has been approved by EMEA since 2001 for prevention of SRE in adult patients with advanced malignancies involving the bone. It has been used extensively for many years and has a well-known toxicity profile. It is not financially possible to conduct a new study where all possible side effects will be reported rigorous, as no pharmaceutical companies have shown interest in the study. Furthermore, it is unlikely that new – still unknown – side effects can be identified from this study since all patients most likely will receive multiple lines of anti-myeloma chemotherapeutics that will differ from site to site, and a significant portion of the patients will die due to progressive disease during the protocol. However, the Nordic Myeloma Study Group finds it very relevant to conduct a study with focus on BON, which is a late occurring, severely disabling side effect where the incidence increases proportionally to the exposure time. In this study, we will focus on BON and renal insufficiency as this is a common clinically relevant side effect to zoledronic acid. Patients will furthermore be evaluated using QoL, which ultimately will answer the question whether prolonged treatment with zoledronic acid is of benefit for these severely ill patients. All AEs and SAEs will be documented in the patient’s medical journal but will not be reported in the CRF if they can be related to the myeloma disease or to the chemotherapeutic treatment the patient receives. All SAR and SUSAR will be reported in the CRF. The treating physician decides if an AE or SAE is related to the investigational compound and thus should be reported as an SAR / SUSAR. Summary of Product Characteristics supplied in appendix 5 will be used as reference document to decide if a SAR should be upgraded to a SUSAR. All cases of renal insufficiency, BON, hypo-, and hypercalcaemia, will be reported in the CRF regardless of causality.

Registration of predefined (section 1.9.1 and 1.9.2) AEs, SAEs, SAR, and SUSARs will continue until the last infusions at year 4 +30 days for the treatment group or until year 4 +30 days for the observation group.

All national SAE, SAR, and SUSARs reported in the CRF during the trial will be listed and reported yearly by the national investigator to the National Health Authority and to the National Ethics Committee according to the national regulations by the national study secretary.

All SUSARs will be listed and reported yearly by the sponsor to the national investigators and to the Danish Health Authorities.

Annually the steering committee will discuss the numbers of SAE, SAR, and SUSARs in the two patient arms. Based on these data the committee will decide if the study should be terminated before time. Likewise an interim analysis will be conducted when half the patients have completed the study. If significant relevant different is observed already at this time-point the study will also be terminated for the benefit of the remaining patients

